#### Process outcomes

For the BCS in the experimental group, technical data on the use of the BREATH intervention will be collected in addition to the standardized questionnaires. Because the actual use of this newly developed intervention in everyday life is unclear, usage variables are recorded to reflect the actual exposure to the intervention content. Frequency and duration of logins, website activity, and other significant usage statistics will be evaluated 
[73].

#### Other outcomes

For all patients, medical disease-specific data will be provided by the hospital where the patient is recruited, or will be collected from the (electronic) medical record by the researcher. Also, in the post-treatment (T1) measure, a question on breast-cancer specific Internet use will be listed.

### Sample size calculation

Based on the two primary outcomes of the BREATH study, effect on patient level is defined as a decrease in psychological distress (as measured with the SCL-90) *or* an increase in empowerment (as measured with the CEQ). Therefore, effectiveness of the BREATH intervention is demonstrated when one of the two effects is significant. Sample size calculation is based on the SCL-90, since the SCL-90 has proven sensitive to change through psychological face-to-face intervention in fatigued cancer survivors 
[36] and information on sensitivity to change of the CEQ is unknown. Significance level of the sample size calculation was adjusted to p ≤ 0.25 to keep the overall chance for type-I errors on 5%. To detect a significant difference (0.25) with 80% power between intervention and control group on the SCL-90, a sample size of 128 BCS (64 in each group) is needed. This sample size calculation is based on a medium effect size of 0.50 of the BREATH intervention, which has proven to be a high effect size for non-guided psychological interventions 
[74]. Based on a systematic review on attrition in randomised controlled trials of Internet interventions for anxiety and depression 
[75], we take into account a 25% study drop-out rate. This results in a maximal sample size of 170 BCS that need to be included in the BREATH trial in case of considerable drop-out.

**Table 2 T2:** Primary and secondary outcome measures of the BREATH study

**Questionnaires**		**Response format**	**Example questions**	**Timepoints**

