### Statistical analysis

A general linear model for repeated measurements (by the method of mixed linear model) will be used to analyze the effect of the BREATH intervention on the two primary outcome variables (distress and empowerment). Chi square (categorical variables), ANOVA (normally distributed continuous variables), and Kruskall-Wallis (non-parametric variables) will be used to asses baseline characteristics between groups. Analysis will be done according to intention-to-treat methodology.

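### The per-outcome significance level is printed twice as 0.25, which contradicts the 5% overall error it is meant to protect and does not yield 64 per arm; the sample size does not settle which level was intended.

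*Protocol article*

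**What the plan says.** All the statements that matter stand in the Protocol article under Sample size calculation.

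- Success rule: "effectiveness of the BREATH intervention is demonstrated when one of the two effects is significant". The two effects are a fall in distress on the SCL-90 and a rise in empowerment on the CEQ.
- Level and its purpose: "Significance level of the sample size calculation was adjusted to p ≤ 0.25 to keep the overall chance for type-I errors on 5" per cent.
- Level repeated beside the power: "To detect a significant difference (0.25) with 80% power between intervention and control group on the SCL-90".
- Effect size: "This sample size calculation is based on a medium effect size of 0.50 of the BREATH intervention".
- Result: "a sample size of 128 BCS (64 in each group) is needed". This is raised to 170 for 25% drop-out.

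The article does not say whether the tests are one- or two-sided. Study design calls the trial a superiority trial, and the hypotheses are worded in the direction of benefit. The value 0.025 appears nowhere in the article. The Statistical analysis section names a mixed linear model "on the two primary outcome variables (distress and empowerment") and prints no level.

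**The concern.** With two chances to succeed, the level for each test must be set below 5% if the overall error is to stay at 5%. The article recognises this and says it made the adjustment, but the printed level is five times the overall target instead of half of it. The sentence therefore contradicts itself, and the repetition in the next sentence leaves no correct figure to set against it.

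The level decides the trial's main claim. If the printed level, the 5% target and the sample size do not agree, a reader cannot tell which threshold was planned. Choosing one after the p-values are known would weaken the conclusion.

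**Working it through.** **Inputs** (all from Sample size calculation, except the 1:1 allocation from Randomization): overall error 5%; two outcomes, either suffices; level 0.25; effect size d = 0.50; power 80%; 64 per arm; drop-out 25%. Sidedness is not given, so both are tried.

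**Step 1: reproduce 64 per arm.** For two means, normal approximation, n per arm = 2 × (z for the level + z for the power)² / d². With d = 0.50 the factor 2/d² is 8, and z for 80% power is 0.8416. The t test figures use the noncentral t distribution.

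- Level 0.25, two-sided: 8 × (1.1503 + 0.8416)² = 31.7, so 32.
- Level 0.25, one-sided: 8 × (0.6745 + 0.8416)² = 18.4, so 19.
- Level 0.05 two-sided, or equally 0.025 one-sided: 8 × (1.9600 + 0.8416)² = 62.8, so 63.
- Level 0.025, two-sided: 8 × (2.2414 + 0.8416)² = 76.0, so 77.

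| Level per outcome | Sides | n per arm, normal | n per arm, t test | Power at 64 per arm, t test |
|---|---|---|---|---|
| 0.25 | two | 32 | 32 | 95.3% |
| 0.25 | one | 19 | 19 | 98.4% |
| 0.05 | two | 63 | **64** | 80.15% |
| 0.025 | one | 63 | **64** | 80.15% |
| 0.025 | two | 77 | 78 | 71.2% |

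The article's 64 reproduces by t test at two-sided 0.05 or one-sided 0.025. It does not reproduce at 0.25, nor at two-sided 0.025. The drop-out step is sound to rounding: 128 / 0.75 = 170.7, against the stated 170.

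**Step 2: could the second 0.25 be a difference instead of a level?** The effect size is given separately as 0.50. A standardised difference of 0.25 would need 127, 252 or 305 per arm at two-sided 0.25, 0.05 or 0.025. None of these is 64, so that reading does not rescue the sentence.

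**Step 3: overall error under the either/or rule.** For independent outcomes with level a on each, the overall error is 1 − (1 − a)².

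- a = 0.25: 1 − 0.75² = 43.75% (upper bound 0.25 + 0.25 = 50%).
- a = 0.25, two-sided, counting only beneficial results: 1 − (1 − 0.125)² = 23.4%.
- a = 0.05: 1 − 0.95² = 9.75%.
- a = 0.025: 1 − 0.975² = 4.94% (upper bound 5%).

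The article gives no correlation between SCL-90 and CEQ. With assumed correlations of magnitude 0.3, 0.5, 0.7 and 0.9, two-sided tests and errors in either direction counted, level 0.25 gives 42.7%, 40.8%, 37.6% and 32.3%; level 0.025 gives 4.8%, 4.7%, 4.3% and 3.6%.

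**Step 4: what two-sided 0.025 would need.** 78 per arm is 156 evaluable. With 25% drop-out, 156 / 0.75 = 208, against 170.

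**The case against.** The strongest reply is that this is a typing slip whose meaning can be read from its own sentence. A level adjusted for two outcomes to hold 5% overall is 0.05 / 2 = 0.025, and nobody would run the analysis at 0.25. That stands as far as it goes: 44% is what the printed text implies, not a likely intention, and a reader should not infer that the trial plans to accept such a rate. But the slip cannot be repaired from the text alone, because a two-sided 0.025 does not give 64 per arm at 80% power.

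A second reply is that one-sided 0.025 reconciles everything: the level, 64 per arm, 80% power and an overall error of 5% in the direction of benefit. The directional hypotheses are compatible with this. It is a fair reading, but the article does not state it, and two-sided 0.05 with no adjustment gives the same 64.

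Two stronger readings are tempting and should be resisted.

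- A reader might infer that the analyst will fall back on two-sided 0.05 per outcome and so nearly double the error, to 9.75%. The article does not support this. It says the level was adjusted, and 64 per arm fits one-sided 0.025 equally well. Moreover, 9.75% counts significant results in either direction; counting only benefit, two-sided 0.05 gives 1 − 0.975² = 4.94%.
- A reader might treat the absence of a level under Statistical analysis as a defect in itself. A journal article may leave that to the full protocol or analysis plan. Nothing in that section is wrong.

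**Conclusion.** The point holds as an internal contradiction in the decision threshold. As printed, 0.25 per outcome gives an overall error of 43.75% under independence, 32% to 43% for assumed correlations of 0.9 to 0.3, and 23.4% if the tests are independent and two-sided and only benefit counts. None of these is near 5%. Nor does 0.25 give the stated sample size.

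The intended figure is very probably 0.025. What stays open is sidedness, and it matters: at 64 per arm and d = 0.50, power is 80% if 0.025 is one-sided and 71% if it is two-sided. These power figures rest on a two-sample t test with 64 evaluable women per arm; the planned mixed model may differ somewhat. The error and the open sidedness should be resolved before the data are analysed.

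**What to change.** In Sample size calculation, replace both occurrences of 0.25 by 0.025, say that this level governs the tests of SCL-90 and CEQ, and state whether the tests are one- or two-sided. Then reconcile the sample size:

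- If two-sided, restate the power at 64 per arm as about 71% in place of 80%. Keeping 80% would need 78 per arm, that is 156 evaluable and 208 with 25% drop-out.
- If one-sided, say so and note that the 5% overall error is one-sided. The figures 128 and 170 can then stand.

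Holm's step-down (smaller p-value at 0.025, then the other at 0.05) is optional. It cannot change the either/or conclusion, because the first step already decides it. Its gain is limited to the second outcome: 80% power there is conditional on the other outcome having been significant. If both effects are 0.50 and independent, an outcome's overall power is 0.712 + (0.8015 − 0.712) × 0.712, or about 78%.

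The correction itself costs two figures and a sentence or two. The real price arises only if the tests are two-sided: a less favourable stated power, or a larger sample.

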### Hypotheses of the BREATH trial

The primary objective of this randomised controlled trial (RCT) is whether the BREATH intervention is effective compared to usual care in fostering adjustment after curative breast cancer treatment by reducing psychological distress and improving empowerment in BCS. Because BSC with and without elevated levels of psychological distress are included it is hypothesized that through using the BREATH intervention:

1) *distressed* BCS will experience a decrease in psychological distress,

2) *non-distressed* BCS will maintain a low level of distress, and/or

3) both *distressed* and *non-distressed* BCS will increase in empowerment.

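### If the even split of the 5% error between the two primary outcomes is carried into the analysis, Holm's step-down rule would give the same protection and a better chance of claiming both effects

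*Protocol article*

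**What the plan says.** Under Hypotheses of the BREATH trial, the primary objective is to foster adjustment "by reducing psychological distress and improving empowerment in BCS". The hypotheses listed there make separate statements on distress and on empowerment, joined by and/or.

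Under Sample size calculation, success is defined more loosely: "effectiveness of the BREATH intervention is demonstrated when one of the two effects is significant". For multiplicity, the section states "Significance level of the sample size calculation was adjusted to p ≤ 0.25", with the purpose "to keep the overall chance for type-I errors on 5" percent. The same figure returns in the power statement: "To detect a significant difference (0.25) with 80% power between intervention and control group on the SCL-90". The result is 128 evaluable women (64 per group), or 170 with 25% drop-out. On effects: "This sample size calculation is based on a medium effect size of 0.50 of the BREATH intervention"; for the CEQ, "information on sensitivity to change of the CEQ is unknown".

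Under Statistical analysis, a mixed linear model is planned "on the two primary outcome variables (distress and empowerment"). That section gives no significance level and no rule for testing the two outcomes together. The article neither mentions nor excludes a step-down rule.

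**The concern.** One lowered level for two outcomes, meant to hold 5% overall, is an even (Bonferroni) split. It is the only multiplicity device in the article. If it governs the analysis, the second outcome must still pass at 0.025 after the first has been shown, and the 5% aim does not require that.

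At stake are the separate claims. Take p = 0.01 on the SCL-90 and p = 0.04 on the CEQ. Under the split only the distress effect can be claimed. Under Holm both can, at the same overall 5%. The objective names both outcomes, so readers will want to know which of them was shown.

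**Working it through.** **Inputs from the article.** Two primary outcomes; overall error 5%; effect d = 0.50 on the SCL-90; 64 evaluable per group; 1:1 allocation; 25% drop-out.

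**Assumptions, not in the article.** Two-sided tests; level 0.025 in place of the printed 0.25; CEQ effect 0.50, varied from 0.1 to 0.5; correlation between the outcomes 0 to 0.7; a simple two-group comparison standing in for the mixed model.

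**1. The plan's own figure.** n per group = 2(z_α + z_0.80)²/d², with d = 0.50 and z_0.80 = 0.842:

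- 0.05 two-sided (the same as 0.025 one-sided): 2(1.960 + 0.842)²/0.25 = 62.8, so 63, or 64 by the t test. This reproduces 128.
- 0.025 two-sided: 2(2.241 + 0.842)²/0.25 = 76.0, so 77, or 78 by the t test.
- 0.25 two-sided, as printed: 2(1.150 + 0.842)²/0.25 = 31.7, so 32.

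Drop-out: 128/0.75 = 170.7, in line with 170.

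**2. Why 0.25 is read as 0.025.** Two independent tests at 0.25 give 1 − 0.75² = 43.75% overall error. At 0.025 they give 1 − 0.975² = 4.94%.

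**3. Holm holds 5%.** With both nulls true, a false claim needs the smaller p ≤ 0.025, which has probability at most 0.025 + 0.025 = 0.05 for any correlation. With one null true, a false claim needs that outcome's p ≤ 0.05, again at most 5%. Simulation with 200,000 trials gave 4.96% (both null, correlation 0), 4.70% (both null, correlation 0.5) and 4.3% (one null, correlation 0).

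**4. Gain by hand, correlation 0.** The mean of each test statistic is d√(n/2) = 0.50 × √32 = 2.828.

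- Power of one outcome at 0.025: Φ(2.828 − 2.241) = 0.7214.
- Power of one outcome at 0.05: Φ(2.828 − 1.960) = 0.8074.
- Both shown, split: 0.7214² = 52.0%.
- Both shown, Holm (both p ≤ 0.05 and at least one ≤ 0.025): 0.8074² − (0.8074 − 0.7214)² = 0.6519 − 0.0074 = 64.5%.
- Gain: 12.4 points before rounding.

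**5. Gain by t-test simulation, effect 0.50 on both outcomes, 64 per group.**

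| Correlation | Both, split | Both, Holm | Gain (points) | At least one (either rule) |
|---|---|---|---|---|
| 0 | 50.6% | 63.4% | 12.8 | 91.6% |
| 0.3 | 54.1% | 65.7% | 11.5 | 88.0% |
| 0.5 | 57.2% | 67.8% | 10.6 | 85.2% |
| 0.7 | 60.4% | 70.0% | 9.7 | 82.0% |

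The chance of showing the SCL-90 effect itself rises from 71% to 76–77%. If the tests are read as one-sided, the gain in showing both is 12.0, 10.7, 9.8 and 8.7 points (normal approximation).

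**6. Smaller CEQ effects** (SCL-90 effect 0.50, correlation 0.5, normal approximation).

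| CEQ effect | Both, split | Both, Holm | Gain (points) |
|---|---|---|---|
| 0.1 | 4.5% | 7.9% | about 3 |
| 0.2 | 12.6% | 19.2% | about 7 |
| 0.3 | 26.5% | 36.2% | about 10 |
| 0.4 | 43.6% | 54.6% | about 11 |
| 0.5 | 58.4% | 68.7% | about 10 |

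**7. No drop-out.** With 85 per group (170/2), effect 0.50 on both and correlation 0.5, both are shown in 75.2% (split) against 83.1% (Holm), a gain of 8 points.

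**The case against.** The strongest objection is that the article does not state the rule criticised here. The lowered level belongs to the sample size calculation, and the analysis section is silent. A plan using Holm could also size one outcome at half the family level, because the smaller p value is tested there first. A condensed article may leave the testing procedure to a statistical analysis plan that is not shown. All of this stands. A reader might infer that the plan has fixed 0.025 for each outcome in the final analysis; the text does not say so. The point is therefore conditional on the split being carried over, and the silence itself is not counted as a fault.

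Second, an even split is valid and standard, and its confidence intervals match the tests simply. That also stands: the issue is efficiency, not validity.

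Third, success needs only one significant effect, and for that Holm gains nothing. This is correct, because the first step of Holm is the split itself. What remains is the gain in the separate claims on distress and empowerment, which the hypotheses make one by one.

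Fourth, the size of the gain rests on a CEQ effect and a correlation that the article does not give. This stands too, so the gain is shown as a range.

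**Conclusion.** The point holds in conditional form. If the even split is used in the analysis, it is stricter than the 5% aim requires for the second outcome. Holm gives the same protection under any correlation and rejects everything the split rejects.

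The gain in showing both effects is about 10 to 13 points with 64 per arm, two-sided tests, effects of 0.50 on both outcomes and correlation 0 to 0.7. At correlation 0.5 it falls to about 7 points for a CEQ effect of 0.2 and 3 points for 0.1. The CEQ effect, the correlation, the sidedness and the 0.025 level are assumptions.

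Two stronger readings are not supported. A reader might infer that the trial loses power for its declared success criterion; it does not. A reader might also infer that Holm repairs the sample size paragraph. It does not correct the printed 0.25. Nor does it remove the mismatch between 128 patients and a two-sided 0.025 level, at which SCL-90 power is about 71–72%. Those are separate points.

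**What to change.** State the testing rule in the Statistical analysis section, for example: *The two primary p values are tested by Holm's procedure at an overall two-sided 5% level: the smaller at 0.025 and, if it is significant, the larger at 0.05. Effects on distress and on empowerment are claimed separately by this rule.* If a statistical analysis plan already says this, the article's wording need only agree with it.

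The cost is one sentence, fixed before the data are analysed, with no added patients or measurements. The small downside is that confidence intervals matching a step-down rule are less simple; ordinary 95% intervals can be reported beside the adjusted p values.

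### The printed significance level of 0.25 cannot hold the overall error at 5% or give 64 per arm, and sidedness is unstated: at two-sided 0.025 an unadjusted SCL-90 comparison has about 71% power, at one-sided 0.025 the stated 80%

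*Protocol article*

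**What the plan says.** All the relevant figures are in the Sample size calculation section of the protocol article.

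- There are two primary outcomes, distress (SCL-90) and empowerment (CEQ), and "effectiveness of the BREATH intervention is demonstrated when one of the two effects is significant".
- On the level: "Significance level of the sample size calculation was adjusted to p ≤ 0.25 to keep the overall chance for type-I errors on 5" (per cent). The value 0.25 appears again in brackets in the next sentence, beside the difference to be detected.
- On the size: "with 80% power between intervention and control group on the SCL-90, a sample size of 128 BCS (64 in each group) is needed".
- On the effect: "This sample size calculation is based on a medium effect size of 0.50 of the BREATH intervention".
- On attrition, 25% drop-out is allowed for: "This results in a maximal sample size of 170 BCS that need to be included in the BREATH trial in case of considerable drop-out".

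Randomization gives 1:1 allocation. Statistical analysis names a mixed linear model for repeated measurements and intention-to-treat. Neither that section nor the sample size section says whether the tests are one- or two-sided.

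**The concern.** When either of two outcomes is enough for success, each must be tested at a reduced level if the overall error is to stay at 5%. The article says this reduction was made in the sample size calculation. However, the level it prints is far too large for that purpose, and the sample size it prints does not follow from that level.

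Reading 0.25 as a slip for 0.025 repairs the error claim. It leaves a second question, because 64 per arm for an effect of 0.50 is the familiar answer for a single two-sided test at 5%, with no adjustment.

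Two things are at stake. A reader cannot tell from the article which threshold an outcome must meet for the trial to claim success. And if tests are two-sided at 0.025, a null SCL-90 result would be read against more power than this calculation supports.

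**Working it through.** **Inputs.** From Sample size calculation: standardised effect d = 0.50, power 80%, 64 per arm, 25% drop-out, overall error 5%, success on either of two outcomes. From Randomization: 1:1 allocation. Not given: sidedness and any baseline-to-follow-up correlation.

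**1. Can 0.25 hold 5% overall?** For two either-or tests at level a, the overall error is at most 2a, and 1 − (1 − a)² if they are independent.
- a = 0.25: at most 0.50; independent 1 − 0.75² = 0.4375.
- a = 0.025: at most 0.05; independent 1 − 0.975² = 0.0494.

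So 0.25 fails, and 0.025 is the level that fits the claim.

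**2. Which level gives 64 per arm?** In the normal approximation, n per arm = 2(z_α + z_power)²/d², with z_power = 0.8416. The t column uses the noncentral t distribution.

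| Level per test | n/arm, normal | n/arm, t | Power at 64/arm, t |
|---|---|---|---|
| 0.05 two-sided | 63 | 63.8 → 64 | 80.1% |
| 0.025 one-sided | 63 | 63.8 → 64 | 80.1% |
| 0.025 two-sided | 77 | 77.3 → 78 | 71.2% |
| 0.05 one-sided | 50 | 50.2 → 51 | 87.9% |
| 0.25 two-sided (as printed) | 32 | 32.0 → 32 | 95.3% |
| 0.25 one-sided (as printed) | 19 | 18.5 → 19 | 98.4% |

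Example, two-sided 0.025: 2(2.2414 + 0.8416)²/0.25 = 76.04, so 77 (78 with the t distribution).

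The plan's 64 is reproduced by two-sided 0.05 and, numerically the same, by one-sided 0.025. It is not reproduced by 0.25 in either form, nor by two-sided 0.025.

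**3. Power at two-sided 0.025 with 64 per arm.** Normal approximation: d√(n/2) = 0.50 × √32 = 2.828; 2.828 − 2.241 = 0.587; Φ(0.587) = 72.1%. The t distribution gives 71.2%. The effect detectable with 80% power is 0.551. A Šidák level (1 − √0.95 = 0.0253) changes little: 71.4%.

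**4. Drop-out.** The plan's figure: 128/0.75 = 170.7, which agrees with 170 to within rounding. For 78 per arm: 156/0.75 = 208. With 170 randomised, 156 analysed requires drop-out of at most 1 − 156/170 = 8.2%.

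**5. Baseline adjustment (assumption; the article gives no correlation).** With correlation r between T0 and T1, the effective d is 0.50/√(1 − r²). At 64 per arm and two-sided 0.025, power is 76% at r = 0.3, 80% at r = 0.42 (effective d = 0.50/0.9075 = 0.551) and 84% at r = 0.5.

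**The case against.** The strongest counter-argument is that 64 per arm is also exactly the one-sided 0.025 figure. On that reading 0.025 per outcome, 80% power, d = 0.50 and 64 per arm all agree, two such tests hold the overall one-sided error at 5%, and the only mistake is a slipped decimal. The text lends this some support: the hypotheses and the definition of effect are directional (distress falls, empowerment rises), and the trial is described as a superiority trial.

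This argument stands to the extent that a power shortfall is not established. It does not settle the matter the other way either. Directional wording is normal in a superiority trial and does not declare a one-sided test. Two-sided testing is the usual default when nothing is said, and a 5% error that is one-sided needs to be declared as such. The printed 0.25 is wrong on every reading.

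A reader might go further and infer that the adjustment was forgotten and that the trial as a whole has 71% power. The document does not support that. It never says the calculation used two-sided 5%. The 71% belongs to an unadjusted two-sample comparison of the SCL-90, whereas the planned analysis is a repeated-measures mixed model whose power depends on correlations not given. Nor is 71% the probability that the trial succeeds, because the CEQ gives a second route to success.

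**Conclusion.** The level, power and sample size in this section do not fit together as printed. One error is certain: 0.25, printed twice, would allow an overall error of up to 50% and does not give 64 per arm. Only 0.025 per outcome agrees with the 5% claim.

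The effect on power is conditional on the unstated sidedness:
- **Two-sided 0.025:** about 71% power rather than 80%, a shortfall of about 9 percentage points and of 14 participants per arm (78 − 64). This assumes d = 0.50, 128 analysed and no baseline adjustment.
- **One-sided 0.025:** the 80% and the 64 per arm are correct, with an overall error of 5% one-sided.

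The two-sided case is the likelier reading by convention, but the article does not establish it. On the two-sided reading there is little room to assume a larger effect, since the article itself regards 0.50 as high for a non-guided intervention.

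**What to change.** In the Sample size calculation section:

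1. Correct 0.25 to 0.025 in both places.
2. State whether each primary outcome is tested one- or two-sided.
3. Restate the power to match. If two-sided: 128 analysed participants give about 71% power for d = 0.50 in an unadjusted SCL-90 comparison. If one-sided: 80% stands, with the overall error declared as 5% one-sided.

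Optionally, if the sponsor prefers to state power for a baseline-adjusted analysis, the assumed T0–T1 correlation should be given explicitly with its source.

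The cost is a few sentences and, on the two-sided reading without baseline adjustment, a less favourable power statement. No extra patients are needed to correct the text.
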